## INTRODUCTION

Systemic lupus erythematosus (SLE) is a chronic multi-system autoimmune disease, with a mosaic of phenotypes spanning from mild musculoskeletal and mucocutaneous manifestations to life-threatening organ involvement. While SLE frequency shows worldwide variability attributed to genetic, environmental exposure, diagnostic and methodological differences,^1^ prevalence estimates in Greece range between 39.5 to 123.4 per 100,000 adults.^2–4^

Despite advances in the disease management, significant challenges still remain.^5^ Thus, lupus patients tend to follow a fluctuating pattern of disease activity, with periods of remission alternating with flares.^6^ Moreover, a sizeable number of individuals may experience periods with persistently active, mild-to-moderate activity. Active disease, typically requiring extended intake of glucocorticoids, carries an increased risk for adverse consequences especially accrual of irreversible organ damage, which is a major driver for excessive morbidity and mortality. Furthermore, SLE patients suffer from impaired health-related quality of life (HRQoL), comparable to their counterparts with diabetes mellitus, myocardial infarction and other chronic disorders.^7^ In fact, HRQoL in SLE shows only partial correlation with disease activity^8^; rather, it may be affected by other factors including long-standing complications (i.e., damage) and fatigue. Indeed, the latter parameter is often under-treated by the physicians due to its subjective nature and multidimensional causes despite the fact it can impact on patient’s work ability and productivity, thus resulting in increased rates of unemployment and absenteeism.^9^

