The concordance between the different indices will be determined using the kappa coefficient and the percentage of agreement. The correlation and the association of the cSLEDAI-2K, SLEDAI-2KG, and PhGA scores with the SDI and selected PRO scores will be examined using the Pearson’s or Spearman’s correlation coefficient and linear regression models, respectively. Logistic regression models, using both the univariable and multivariable approach, will also be used to evaluate the association of patient, disease and treatment characteristics with the presence of at least moderate disease activity, as determined by cSLEDAI-2K and by cSLEDAI-2KG, in the overall study population. In the context of the exploratory objectives, the annual rate of flares, hospitalisations and ED visits with the respective 95% Poisson confidence intervals (CIs) will be estimated. Missing data will be reported. No imputation methods will be performed in regards to missing data with the exception of partial dates which will be defined in more detail in the SAP. With regards to the scoring and handling rules of any missing PRO items, the relevant scoring instructions, where available, will be followed. All statistical tests will be two-sided and performed at a 0.05 significance level.

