### Sample size

In view of the exploratory/descriptive nature of the study and based on practical considerations, a sample size of 200 eligible patients is considered both feasible and sufficient for estimating the primary outcome measures. This number offers a maximum margin of error of 7.1% (with 95% CI using the Clopper-Pearson exact method ranging between 42.9% and 57.1%) for the estimation of a percentage of 50%, which represents a scientifically acceptable level of precision. Also, this sample size ensures that for any of the defined study subpopulations representing at least 50% of the overall population, frequency estimates of interest may be determined with a margin of error not exceeding 10.2%, therefore ensuring sufficient precision to draw meaningful conclusions.

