## DISCUSSION

Herein, we present the rationale and methodology of a multicentre observational study in Greece, which aims to capture the range and impact of disease activity and severity, treatment patterns, and areas of need that exist among individuals with SLE. Previously, a nationwide study of 381 Greek SLE patients followed in seven hospital clinics had reported a high frequency of chronic active (11.6%) and relapsing-remitting (60.6%) disease patterns, as well as of usage of glucocorticoids (66.0%, 22.0% at a dose exceeding 7.5 mg/day prednisone equivalent) and immunosuppressive or disease-modifying antirheumatic agents (97%).^36^ Of note, the aforementioned study was enriched in patients with active disease (ascertained by change or intensification in therapy) and abnormal lupus serology (increased anti-dsDNA autoantibodies and/or low serum C3/C4 levels). Due to its explicit design and inclusion criteria, the NYMERIA study seeks to obtain more generalisable, contemporary estimates of the disease activity and severity of SLE patients managed in Greece, the use of various treatment modalities (including biologics) while also, addressing the patient perspective through relevant PROs.

Collecting data on real-world management practices and their outcomes help to bridge the knowledge gap between clinical research which is conducted in the strict environment of controlled randomised settings and that performed in daily clinical practice. The latter follow less restrictive methodological standards regarding patient selection, treatment, and other design aspects. Consequently, their results are often more generalisable, particularly for populations with complex diseases like SLE. Their cross-sectional aspect can provide a snapshot-based approach to document prevalence rates and other outcomes of interest for subgroups of population at a given timepoint in a routine clinical practice setting, which can be used on the planning of health services or the determination of healthcare practices, while being less resource-demanding and less time-consuming compared to other study designs. To this end, and despite variations in the methodology and reported outcomes, observational studies from Europe and the United States have been valuable in demonstrating that insufficiently controlled disease is not uncommon in SLE therefore, highlighting the need for novel, more effective treatment modalities and strategies.^37–42^

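### The exploratory annual rates of flares, hospitalisations and ED visits get plain Poisson intervals, which are too narrow if event rates differ between patients; low priority

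*Protocol article*

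**What the plan says.** In the protocol article, the text after Table 1 under Study outcomes and statistical analysis sets the method: "the annual rate of flares, hospitalisations and ED visits with the respective 95% Poisson confidence intervals (CIs) will be estimated". It places these rates among the exploratory aims of the study. No scale factor, robust variance or negative binomial model is mentioned. The same paragraph leaves the handling of partial dates to the SAP, but not the choice of this interval.

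Two other places describe how patients differ:

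- The Introduction says that "lupus patients tend to follow a fluctuating pattern of disease activity, with periods of remission alternating with flares". It adds that a sizeable number go through periods of persistently active disease.
- The Discussion cites an earlier Greek cohort with "a high frequency of chronic active (11.6%) and relapsing-remitting (60.6%) disease patterns".

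Data sources and instruments gives a 12-month look-back for hospital-based resource use. The planned sample is 200 patients.

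**The concern.** The study aims at a representative sample of outpatients, so the target is the mean rate in the population from which they come. The uncertainty of that estimate has two parts: chance in each patient's count, given that patient's own rate, and chance in which patients, with which rates, were sampled. A Poisson interval contains only the first part. It is right only if every patient has the same rate, so that the variance of the counts equals their mean.

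Some patients are persistently active, some relapse and remit, and others do neither, so a common flare rate is not credible. The reported intervals would then claim more precision than the data carry. The Abstract and Introduction say the study's data may inform reimbursement and health technology assessment. Event rates are a natural burden input there, although the article does not single these rates out for that use.

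**Working it through.** **The plan's own figures.** The article states no precision for the event rates. It does so for proportions: "This number offers a maximum margin of error of 7.1% (with 95% CI using the Clopper-Pearson exact method ranging between 42.9% and 57.1"%, and for a subpopulation of at least half the sample "with a margin of error not exceeding 10.2"%. Both reproduce with exact Clopper-Pearson limits: 100/200 gives 42.87% to 57.13% (7.1 points) and 50/100 gives 39.83% to 60.17% (10.2 points). They concern proportions and are not affected by this point.

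**Inputs from the article.** n = 200 and a 12-month look-back for hospital-based resource use. Inclusion requires a disease duration of at least 12 months, so roughly equal person-time is reasonable: 200 × 1 = 200 person-years.

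**Assumptions.** The look-back for flares is also 12 months. The event rate μ is 0.2, 0.6 or 1.0 per patient-year. Patient rates follow a gamma distribution with mean μ and shape a = 2, 1 or 0.5; a smaller shape means more difference between patients.

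**Formulas.**
- Variance/mean ratio of the counts: φ = 1 + μ/a.
- Required width relative to Poisson: √φ.
- Approximate coverage of the Poisson interval: 2Φ(1.96/√φ) − 1.
- Simulated coverage: exact chi-square Poisson interval on the total count, 6,000 simulated studies per scenario.

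| μ per year | shape a | φ | width factor √φ | approximate coverage | simulated coverage |
|---|---|---|---|---|---|
| 0.2 | 2 | 1.1 | 1.05 | 93.8% | 95.4% |
| 0.2 | 1 | 1.2 | 1.10 | 92.6% | 93.9% |
| 0.2 | 0.5 | 1.4 | 1.18 | 90.2% | 92.1% |
| 0.6 | 2 | 1.3 | 1.14 | 91% | 91.8% |
| 0.6 | 1 | 1.6 | 1.26 | 88% | 88.3% |
| 0.6 | 0.5 | 2.2 | 1.48 | 81% | 82.3% |
| 1.0 | 2 | 1.5 | 1.22 | 89.0% | 89.6% |
| 1.0 | 1 | 2.0 | 1.41 | 83.4% | 84.1% |
| 1.0 | 0.5 | 3.0 | 1.73 | 74.2% | 74.8% |

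A separate run of 20,000 studies per scenario gave 95.0%, 93.7% and 91.8% at 0.2 per year, and 89.2%, 84.2% and 75.1% at 1.0 per year. With no dispersion, coverage at n = 200 was 95–96%, so the shortfall comes from the dispersion and not from the exact interval. Sample size does not cure it: at 1.0 per year and shape 0.5, n = 100 gives 75.3% and n = 200 gives 75.1%.

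**Illustration with the Discussion's shares.** Chronic active is 11.6%, relapsing-remitting 60.6%, and the unlabelled remainder 100 − 11.6 − 60.6 = 27.8%. Assume flare rates of 2, 1 and 0 per year:
- mean = 0.116 × 2 + 0.606 × 1 = 0.838
- mean of squares = 0.116 × 4 + 0.606 × 1 = 1.070
- between-patient variance = 1.070 − 0.838² = 0.368
- φ = 1 + 0.368/0.838 = 1.44, width factor 1.20, coverage about 90%

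With the rates halved (1, 0.5, 0), φ is 1.22 and coverage about 92%.

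**What a reader would see.** For 100 events in 200 person-years (0.50 per year), the exact Poisson interval is 0.41 to 0.61. By normal approximation, 0.50 ± 1.96 × √(100φ)/200 gives 0.38 to 0.62 at φ = 1.5, 0.36 to 0.64 at φ = 2, and 0.33 to 0.67 at φ = 3.

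**The case against.** The best defence is that this is a descriptive study, that these rates are exploratory and absent from Table 1, and that no decision or sample size rests on their intervals. That stands, and it sets the priority.

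The evidence for heterogeneity is also indirect, and this stands in part. The Discussion's cohort reports course patterns rather than flare counts, and it was enriched for active disease. Chronic active disease need not produce more discrete flares. The Introduction's alternation of remission and flare describes change within a patient. For hospitalisations and ED visits the article describes no clustering. If the records held at most one event per patient, the variance would even fall below the mean. But the argument needs only that patients' rates differ, and an article that distinguishes persistently active from relapsing-remitting patients supports that for flares.

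The unseen SAP could add a dispersion adjustment. That limits confidence, but the article names Poisson as the method, so this is a stated choice and not a detail left open.

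Four stronger readings are tempting but unsupported:

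- **All three intervals miss the true rate far more often than 5% of the time.** At about 0.2 events per year coverage is still 92–95% in the scenarios above, so rare events may be little affected.
- **The subpopulations are equally affected.** The Table 1 footnote on subpopulations covers the outcomes in that table, and the article does not say the event rates will be split.
- **Clustering by site makes it worse.** With 12 sites this is plausible, but nothing in the article allows it to be quantified.
- **The article describes a quiescent group that supplies the zero counts.** The remaining 27.8% is not labelled; the rate of 0 above is an assumption.

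**Conclusion.** The point holds in direction: a plain Poisson interval is too narrow when rates differ between patients, and the article gives reason to expect this for flares and, by inference, for hospitalisations and ED visits. Its size is conditional on the assumed rates and dispersion. Over the assumed range it runs from negligible for rarer events with mild dispersion to substantial for frequent, strongly dispersed ones: coverage from about 95% down to about 75%, with a required width about 1.05 to 1.7 times that planned. The rates themselves are not biased by this. The primary proportions, their Clopper-Pearson intervals and the statement that "a sample size of 200 eligible patients is considered both feasible and sufficient for estimating the primary outcome measures" are untouched. It is a low-priority correction.

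**What to change.** In Study outcomes and statistical analysis, replace the Poisson interval with a 95% interval that allows for overdispersion, chosen before the data are seen. Any of these will do:

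- a quasi-Poisson or robust-variance interval;
- a negative binomial model with log person-time as offset;
- a bootstrap that resamples patients.

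Report the variance/mean ratio of the counts for each event type, so that readers can see whether the adjustment mattered.

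The change is one line in the text and a small change in the program. The quasi-Poisson, robust and bootstrap options leave the estimated rates unchanged, as does the negative binomial with equal 12-month person-time. The downside is somewhat wider intervals; if the counts turn out not to be overdispersed, almost nothing is lost.

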### Methods to minimise bias

To lessen confounding due to the potential of patient selection bias, a consecutive sampling process will be utilised. Physicians will be requested to provide documentation of the screening process results for both consented and non-consented patients. Patient information/recall bias during collection of PRO data will be avoided by the use of widely used tools that rely on a relatively short-term (i.e., one week for FSS and WPAI:Lupus, and 4 weeks and 3 months for the LupusPRO) or no recall period (for the EQ-5D-5L). Additionally, patients should complete the self-administered PROs on their own before any study-specific procedures or clinical assessments are performed, and before they are informed about their disease status or any changes to their current treatment (where applicable). This approach is intended to prevent any response bias.

### Sample size

In view of the exploratory/descriptive nature of the study and based on practical considerations, a sample size of 200 eligible patients is considered both feasible and sufficient for estimating the primary outcome measures. This number offers a maximum margin of error of 7.1% (with 95% CI using the Clopper-Pearson exact method ranging between 42.9% and 57.1%) for the estimation of a percentage of 50%, which represents a scientifically acceptable level of precision. Also, this sample size ensures that for any of the defined study subpopulations representing at least 50% of the overall population, frequency estimates of interest may be determined with a margin of error not exceeding 10.2%, therefore ensuring sufficient precision to draw meaningful conclusions.

## CONDUCT OF THE STUDY AND REGULATORY ASPECTS

Before the first subject is enrolled in this study and any study-related procedures are undertaken the following should be fulfilled: a) written approval of the study by the Ethics Committee/Institutional Review Boards of the participating Hospitals, according to local regulations; and b) agreements between the sponsor (AstraZeneca) and each Investigator/Institution are signed. Upon the enrolment of each subject into the study, the participating physician shall review of patient’s medical history and current treatment, in order to confirm if eligibility criteria are met, explain the aims of the study to the patient, obtain signed informed consent, followed by collection of the data through routine clinical assessments, medical chart review, patient self-report and self-administered PROs, and completion of the electronic case report forms (eCRFs).

A subject will be withdrawn from data collection within the study in case of patient’s withdrawal of informed (at any time and for any reason) or erroneous enrolment (i.e., the subject does not meet the eligibility criteria for participation in the study).

The study will use eCRFs provided by the Sponsor through a dedicated system. The eCRF system, designed by a qualified contract research organisation (CRO), adheres to data protection regulations. Patients will be identified by unique numbers. Investigators or authorised personnel will enter data following the Investigator Instructions Manual. Data will be immediately saved and tracked for changes. Upon completion, the eCRF will be electronically signed by the Investigator, and a copy will be archived on-site. Quality control mechanisms will ensure data integrity, outlined in the study-specific monitoring, data management, validation plans, and SAP. Real-time edit checks will handle discrepancies, and source data verification during monitoring visits will mini-mise transcription errors. Statistical analysis and Clinical Study Report (CSR) development will be performed by a designated CRO. Before final database lock, a comprehensive SAP will be drafted, including statistical software and data imputation methods. Electronic archives of all statistical programming and related documents will be maintained. e-CRF archival for each site will be distributed on CD-ROMs or USB sticks after study completion. The designated CRO will review eCRF data for completeness and accuracy, following the DVP. Medical plausibility checks will be conducted by the Sponsor’s personnel. Monitoring, telephone contacts, and on-site visits will ensure study oversight.

## DISCUSSION

Herein, we present the rationale and methodology of a multicentre observational study in Greece, which aims to capture the range and impact of disease activity and severity, treatment patterns, and areas of need that exist among individuals with SLE. Previously, a nationwide study of 381 Greek SLE patients followed in seven hospital clinics had reported a high frequency of chronic active (11.6%) and relapsing-remitting (60.6%) disease patterns, as well as of usage of glucocorticoids (66.0%, 22.0% at a dose exceeding 7.5 mg/day prednisone equivalent) and immunosuppressive or disease-modifying antirheumatic agents (97%).^36^ Of note, the aforementioned study was enriched in patients with active disease (ascertained by change or intensification in therapy) and abnormal lupus serology (increased anti-dsDNA autoantibodies and/or low serum C3/C4 levels). Due to its explicit design and inclusion criteria, the NYMERIA study seeks to obtain more generalisable, contemporary estimates of the disease activity and severity of SLE patients managed in Greece, the use of various treatment modalities (including biologics) while also, addressing the patient perspective through relevant PROs.

Collecting data on real-world management practices and their outcomes help to bridge the knowledge gap between clinical research which is conducted in the strict environment of controlled randomised settings and that performed in daily clinical practice. The latter follow less restrictive methodological standards regarding patient selection, treatment, and other design aspects. Consequently, their results are often more generalisable, particularly for populations with complex diseases like SLE. Their cross-sectional aspect can provide a snapshot-based approach to document prevalence rates and other outcomes of interest for subgroups of population at a given timepoint in a routine clinical practice setting, which can be used on the planning of health services or the determination of healthcare practices, while being less resource-demanding and less time-consuming compared to other study designs. To this end, and despite variations in the methodology and reported outcomes, observational studies from Europe and the United States have been valuable in demonstrating that insufficiently controlled disease is not uncommon in SLE therefore, highlighting the need for novel, more effective treatment modalities and strategies.^37–42^

In SLE, permanent organ damage (quantified by the SDI) has emerged as a powerful determinant of multiple adverse patient outcomes including excessive morbidity and healthcare utilisation, impaired HRQoL, and premature death.^36,43^ Consequently, prevention of damage accrual has been recognised as a distinct therapeutic goal in SLE, which can be facilitated by lowering disease activity, minimising exposure to glucocorticoids and controlling comorbidities.^44^ In agreement with worldwide estimates, earlier findings from single centres in Greece have suggested that organ damage may accumulate at a rate of 18% within the first 6 months following SLE diagnosis,^45^ with this figure rising to 32% after an average disease duration of 7 years.^4^ The current study will provide updated rates of damage in a representative group of SLE patients managed at real-life setting, with the possibility to stratify results according to pertinent demographic and disease characteristics.

There is often discordance between physicians and SLE patients in terms of the activity and status of the disease,^46^ which denotes the necessity that patient perspectives are also taken into consideration especially in the context of shared decision-making process.^16^ Notably, the unpredictable nature of SLE, along with its physical and emotional impact, may significantly impact the overall well-being and quality of life for individuals with SLE.^47^ Furthermore, a complex interplay has been reported between disease-intrinsic characteristics (e.g., type and severity of manifestations), organ damage, treatment-related harms, pain, fatigue, psychosocial factors, and mental disorders with HRQoL, work ability and productivity, which denotes the importance of holistic approach to these patients.^47–52^ Our research marks a significant milestone as it unveils novel insights into patient-reported measures, including HRQoL, fatigue, and work productivity among SLE patients managed in Greece. Results will shed light on these crucial aspects within the country context, further enhancing our understanding of the impact of SLE on patients’ daily lives. The study faces potential errors due to incomplete or inaccurate patient record data, leading to hidden biases. Efforts to mitigate this include requiring sufficient medical records for study eligibility and setting a threshold for missing data in multivariable models. If a subpopulation falls below 100 patients, there may be a significant margin of error, thus affecting the validity of results. Nonetheless, any real-world evidence generated outside the study’s primary aim can be valuable. The observational nature of the study may introduce confounding factors, which will be analysed through appropriate multivariable analyses. Unmeasured confounding will be qualitatively discussed in the results. Internal validity is maintained through source data verification and quality assurance. Generalisability is enhanced by enrolling patients from diverse locations in Greece, though non-probability sampling makes the study’s overall generalisability less robust. Despite these limitations, the value of such studies lies in their ability to provide real-world evidence by capturing data generated during routine clinical care. This makes them more representative of the study population and the observed outcomes compared to randomised controlled trials, which offer information on a select group of patients chosen based on strict and narrow eligibility criteria and treated in a controlled environment.

In conclusion, the NYMERIA multicentre study aspires to contribute to our knowledge of the disease burden and unmet needs among Greek SLE patients by assessing objective disease indices, the usage of therapies and a number of validated PROs. This collaborative and multi-faceted approach could help foster a more nuanced and tailored approach to addressing the challenges faced by SLE patients and healthcare providers alike.
